## Abstract

**Background:**

Diabetes is increasing in incidence, morbidity and treatment costs globally, hence prevention strategies need to be explored. Animal studies and some human data have shown that zinc can improve glycaemic control, but the impact of this effect in a pre-diabetic population remains uncertain. This study is designed to investigate whether zinc gluconate and lifestyle coaching can improve glucose handling and ultimately reduce diabetes incidence in an at-risk pre-diabetic population in Australia.

**Methods/design:**

The study will be a randomised, placebo-controlled, double-blind clinical trial. The study will be conducted at the Hunter New England Local Health District New South Wales (NSW), Australia. Pre-diabetic (haemoglobin A1c [HbA1c] 5.7–6.4) male and female participants (n = 410) aged 40–70 years will be recruited through the Diabetes Alliance Network, a collaboration of diabetes specialists and general practitioner practices. All participants will be given routine care to encourage healthy lifestyle changes using a telephone coaching service (Get Healthy Information and Coaching Service, NSW Health) and then randomised to receive a supplement, either zinc gluconate (equivalent to 30 mg of elemental zinc) or placebo of identical appearance for 12 months. The identity of the supplements will be blinded to both research personnel and the participants. Participants will be asked to complete medical, lifestyle and dietary surveys and will have baseline and final visits at their general practitioner practice. Primary outcomes will be HbA1c and insulin sensitivity collected at baseline and at 1, 6 and 12 months; secondary outcomes will include fasting blood glucose, fasting cholesterol, blood pressure and body mass index. The primary efficacy endpoint will be judged at 6 months.

**Discussion:**

This study will generate new evidence about the potential for health coaching, with or without zinc supplementation, to improve glucose handling and ultimately to reduce progression from pre-diabetes to diabetes.

**Trial registration:**

Australian and New Zealand Clinical Trials Registry, ACTRN12618001120268. Registered on 6 July 2018.

**Electronic supplementary material:**

The online version of this article (10.1186/s13063-019-3317-4) contains supplementary material, which is available to authorized users.

## Background

The global burden of diabetes (among adults aged 20–79 years) in 2015 was estimated at US 415 million and is expected to rise up to 642 million by 2040 [1–3]. The global health cost in 2015 was approximately US $673 billion with an expected 25.4% increased cost to US $802 billion in 2040 [2]. The number of deaths attributed to diabetes worldwide in 2015 was 5 million [2]. It is known that 90–95% of diabetes cases are type 2 diabetes mellitus (T2DM), which is a preventable and modifiable disease [1]. Pre-diabetes mellitus (PreDM) is a potentially reversible condition of impaired glucose handling. It is increasingly being diagnosed on the basis of a haemoglobin A1c (HbA1c) measurement, given the low coefficient of variation of this test [4]. The natural history of PreDM is variable; progression to T2DM occurs in ~ 25%; the abnormal glycaemic state remains in 50%; and reversion to normal glycaemic state occurs in 25% over 3–5 years [5]. People with PreDM are 5–15 times more likely to develop T2DM and are at increased risk of cardiovascular disease (CVD) [6]. The progression of disease through the pre-diabetic phase provides an opportunity to intervene to reduce or delay the onset of frank diabetes.

Interventions for PreDM are limited. Improving lifestyle factors, such as nutrition and physical activity, and maintenance of healthy weight have been found to reduce the progression from PreDM to T2DM by ~ 50%, although these changes take time to institute and are often difficult to maintain for the long term [7]. Despite the effectiveness of interventions to reduce such risk factors, the prevalence/incidence of obesity and PreDM continues to increase globally and in Australia [2, 8]. Given this trend, additional and complementary treatment options that will prevent, or at least delay, progression of PreDM are needed. Our intervention will involve the referral of all participants to an existing health promotion programme provided by the NSW State Health Department: the Get Healthy Information and Coaching Service [13]. The free telephone coaching service contacts participants on up to 13 occasions over the first 6 months of the study to encourage lifestyle improvements. In addition, participants will be randomised to receive either a zinc or placebo daily supplement.

### Rationale

It has long been known that insulin is stored with zinc in the secretory granules within the beta-cells of the pancreas [9]. Zinc participates in glucose handling in many ways:Zinc is involved in the synthesis, storage and secretion of monomeric insulin, as well as conversion to a dimeric form for storage and secretion as crystalline insulin [10, 11].Zinc is essential in insulin action and carbohydrate metabolism [9].Human islet amyloid polypeptide (HIAPP) is a hormone that is stored with insulin in the secretory granule and is released from the pancreatic beta-cells when blood glucose levels are elevated. Under normal conditions, zinc concentration in the beta-cells is the highest in the human body, and zinc plays a role in keeping glucose levels and HIAPP stabilised. When zinc status is low, HIAPP aggregates into amyloid fibres that in turn become cytotoxic to beta-cells [12].Zinc stimulates two different classes of zinc transporter which enhance glucose-stimulated insulin secretion [14].

Translation of this work to humans has occurred in three ways:Two separate meta-analyses of 25 different small-scale zinc supplementation trials have found a significant reduction in fasting blood glucose and HbA1c, as well as cholesterol, in people with PreDM and metabolic syndrome [15, 16].In prospective longitudinal cohorts, those with the highest quintile of dietary zinc intake have the lowest incidence of diabetes during follow-up [17, 18].A randomised controlled trial of zinc supplementation among people with PreDM reduced progression to diabetes from 25% to 11% over 1 year [1]. However, this study was completed in Sri Lanka, where the dietary intake may be different and the diabetes incidence is high [1, 3].

Given such findings, zinc supplementation may be a useful additional strategy to complement existing effective risk reduction interventions. Our study will add to the limited scientific literature and will be the first randomised placebo-controlled trial of its kind in Australia.

## Methods/design

### Aim

Our study is designed to help patients better manage their own health and prevent T2DM, using an existing and effective lifestyle intervention with and without a low-cost zinc supplement, in an Australian population of men and women with PreDM aged between 40 and 70 years.

### Objectives

#### Primary objective

To determine if the Get Healthy Information and Coaching Service with zinc supplementation over 12 months improves glucose-handling parameters (HbA1c and insulin sensitivity [IS]) (Cohen’s *d* = 0.4) compared with the Get Healthy Information and Coaching Service with placebo supplementation.

#### Secondary objectives

To determine if the Get Healthy Information and Coaching Service with zinc supplementation delays or prevents progression to diabetes mellitus compared with the Get Healthy Information and Coaching Service with placebo supplementation.To determine if the Get Healthy Information and Coaching Service with zinc supplementation improves CVD risk factors compared with the Get Healthy Information and Coaching Service with placebo supplementation.To determine if the Get Healthy Information and Coaching Service alone will improve glucose handling and CVD risk factors compared with each individual’s own baseline (within control group only).To determine if the Get Healthy Information and Coaching Service can be incorporated into a new model of care of patients with PreDM through general practitioner (GP) practices.To determine the cost-effectiveness of the new model of care (Get Healthy Information and Coaching Service and zinc supplementation) with early intervention.To determine the acceptability of daily zinc supplementation for patients with PreDM.

### Trial design

The study will be a double-blind, randomised, parallel-group, placebo-controlled superiority trial. The allocation ratio will be 1:1 zinc supplementation and placebo, stratified by GP practice and biological sex (male and female). Participants will be followed up at 1 month, 6 months and 12 months. Both treatment arms will be referred to the Get Healthy Information and Coaching Service type 2 diabetes prevention program for the first 6 months of the trial (standard duration of the programme). The schematic of the trial recruitment is provided in Fig 1.

**Fig. 1 Fig1:**
[figure not shown]
Participant timeline. Standard Protocol Items: Recommendations for Interventional Trials (SPIRIT) figure [20] (Additional file 1) for the study schedule of enrolment, interventions and assessments. Baseline assessments will occur at -t_1–0_ prior to allocation. Follow-up will occur at time points between t_1_ and t_5_ (1, 3, 6, 9 and 12 months after allocation). Adverse event monitoring will occur after allocation at t_2_, t_3,_ t_4_ and t_5_ (3, 6, 9 and 12 months); HbA1c, LDL, HDL, total cholesterol, triglycerides, fasting blood glucose and insulin will be collected at –t_1–0_, t_0_ (baseline), t_1_ (1 month) t_3_ (6 months) and t_5_ (12 months). Close-out assessments will occur at t_5_ (12 months)

### Setting

Participants will be selected by the Diabetes Alliance team through GP practices in the Hunter New England Local Health District, NSW, Australia.

### Eligibility criteria

#### Inclusion criteria

To be eligible, men and women aged 40–70 years and with a body mass index (BMI) ≥ 28 kg/m^2^ will be screened for PreDM on the basis of one HbA1c measurement (5.7–6.4 mmol/L) as per the American Diabetes Association guidelines [19]. Potential participants must be willing to enrol in the Get Healthy Information and Coaching Service and not meet any of the exclusion criteria.

#### Exclusion criteria

Potential participants must not have any of the following: a diagnosis of diabetes; taking zinc, calcium or iron supplements; receiving a weight loss medicine or programme; alcohol intake > 20 g/day; impaired hepatic or renal function; lactating, pregnant or planning a family; or a history of any condition that the investigator may consider a contraindication to participation [1].

### Interventions

All participants will be enrolled in the Get Healthy Information and Coaching Service. This is a registered service run by the New South Wales state health department that provides up to 13 telephone calls over 6 months from allied health professionals who provide health information and support participants to achieve a better lifestyle; it focuses on diet, physical activity, smoking cessation and alcohol reduction [13].

The intervention group will receive a daily oral zinc gluconate capsule (30 mg of elemental zinc, provided by Blackmores, Sydney, Australia) to be consumed before breakfast for a period of 12 months. The placebo group will receive a cellulose capsule (appearance identical to the zinc capsule) to be taken similarly.

### Outcomes

#### Primary endpoints

The primary outcomes are fasting blood glucose (FBG) and HbA1c.

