#### Secondary endpoints

The following are secondary endpoints:Progression to diabetes mellitus (based on FBG or HbA1c)CVD risk factors, including, for example, FBG, plasma cholesterol, body weight, BMI, smoking, alcohol consumption, dietary intake, physical activity and blood pressureAcceptability of the supplements, as shown by pill counts and adverse effects.

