### Sample size

The sample size is based on an estimated mean difference in IS of 0.3 (with SD of 0.7, equal to Cohen’s *d* of 0.4) between the intervention and control groups. We will need 164 participants per group to reject the null hypothesis that the intervention and control group means are equal with probability (power) 0.9 and type I error probability (α) of 0.01. Allowing up to 20% loss to follow-up over 1 year, we will need to recruit a total of 410 participants.

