#### Effectiveness of zinc

##### Primary analysis

IS and HbA1c at baseline and at 1, 6 and 12 months will be plotted to assess response trajectories. We will fit a linear mixed model (LMM) with IS or HbA1c measured at 1, 6 and 12 months as the dependent variable and fixed effects for time (categorical predictor), group and time-by-group interaction terms. This will allow us to identify the time points at which maximal group differences are observed, although the primary outcomes will be judged at 6 months. A random intercept will be included to account for repeated measures on participants, and the model will be adjusted for baseline HbA1c or IS, age, sex, physical activity and diet. The LMM uses all available values for each participant and provides robust effect estimates assuming data are missing at random. All statistical analyses will observe the intention-to-treat principle. A significant difference on either of the primary outcomes will be sufficient to declare an effect, although we will also look at consistency in the direction of the secondary outcomes.

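### The Primary endpoints section names FBG and HbA1c, while the abstract, objective and primary analysis name insulin sensitivity and HbA1c

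*Protocol article*

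**What the plan says.** The protocol article describes the primary outcomes in several places, and they do not agree.

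- Primary endpoints: "The primary outcomes are fasting blood glucose (FBG) and HbA1c". No time point is given.
- Abstract, Methods/design: "Primary outcomes will be HbA1c and insulin sensitivity collected at baseline and at 1, 6 and 12 months". The same paragraph makes glucose secondary: "secondary outcomes will include fasting blood glucose, fasting cholesterol, blood pressure and body mass index".
- Primary objective: asks whether coaching "with zinc supplementation over 12 months improves glucose-handling parameters (HbA1c and insulin sensitivity [IS" and attaches a Cohen's *d* of 0.4.
- Secondary endpoints: "CVD risk factors, including, for example, FBG, plasma cholesterol, body weight", so FBG is listed again directly after being called primary.
- Sample size: "The sample size is based on an estimated mean difference in IS of 0.3", with no planning figures for FBG or HbA1c in that section.
- Primary analysis: "We will fit a linear mixed model (LMM) with IS or HbA1c measured at 1, 6 and 12 months as the dependent variable". It adds "although the primary outcomes will be judged at 6 months", and treats significance on one of the two primary outcomes as enough to claim an effect.

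**The concern.** FBG is both primary and secondary. IS, on which the trial is sized and which the primary model analyses, is in neither endpoint list. These statements cannot all be true.

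The success rule makes this more than an editorial matter. Because one significant primary outcome suffices, membership of the pair determines what counts as a positive trial. As the text stands, either an FBG result or an IS result could be presented afterwards as prespecified, with a section of the protocol to cite for it. If the Primary endpoints section were followed literally, the outcome carrying the stated 90% power would not be primary at all.

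**Working it through.** **Step 1. Set the sections side by side.**

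| Section | HbA1c | IS | FBG |
|---|---|---|---|
| Abstract | primary | primary | secondary |
| Primary objective | named | named | not named |
| Primary endpoints | primary | absent | primary |
| Secondary endpoints | absent | absent | secondary |
| Sample size | absent | sizing outcome | absent |
| Primary analysis | modelled | modelled | not modelled |

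The Primary endpoints section is the outlier on FBG and on IS.

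**Step 2. Reproduce the sample size, to confirm which outcome it belongs to.** Inputs from Sample size: difference 0.3, SD 0.7, power 0.9, alpha 0.01, 20% loss. Sidedness is not stated; two-sided is assumed because it reproduces the figure.

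- Normal approximation: n = 2 × (2.576 + 1.282)² × (0.7/0.3)² ≈ 162.0, rounded up to 163 per group.
- Exact two-sample t test (noncentral t): 164 per group, the stated figure.
- Loss to follow-up: 164/0.8 = 205 per group, and 2 × 205 = 410, the stated total.

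The arithmetic is sound and it is for IS.

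**Step 3. Power for the other candidates.**

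- HbA1c: the only planning figure is the *d* of 0.4 in the primary objective. With 164 per group at two-sided 0.01, power at exactly 0.4 is about 85% (0.848 by the t test, 0.852 by the normal approximation). For IS, 0.3/0.7 = 0.43 gives 0.90.
- FBG: no difference or SD is given, so its power cannot be computed.

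**Step 4. What the contradiction does to the decision.**

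| Significant on | Under Primary endpoints | Under abstract, objective and primary analysis |
|---|---|---|
| HbA1c | success | success |
| FBG only | success | failure |
| IS only | failure | success |

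**Step 5. False-positive chance under the either-outcome rule.** Alpha is 0.01 per test. This is the only alpha stated; applying it to each test is an assumption. With independent tests the chance of at least one false positive is 1 − (1 − 0.01)^k.

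- Two outcomes: 1 − 0.99² = 0.0199, about 2.0%.
- Three candidates: 1 − 0.99³ = 0.0297, about 3.0%.
- Under any dependence, three tests cannot exceed 3 × 0.01 = 0.03.

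The contradiction therefore adds at most about one percentage point. The legend to Fig. 1 lists fasting glucose and insulin but no separate IS test, so IS is probably derived from them. FBG and IS would then share data, and the true increase would probably be smaller.

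**The case against.** The strongest reply is that the Primary analysis section is the operative text. It fixes the dependent variables, the model, the time point and the decision rule. The abstract and the primary objective agree with it on the pair, and the sample size is built on IS. On that view the one sentence under Primary endpoints is a drafting slip. Nothing in the article names three primaries or permits switching, the trial was registered before recruitment began, and the analyst is to be blinded. This stands as the likely explanation, and it shows which pair the rest of the article supports. It does not remove the contradiction, because the section that formally defines the endpoints is the one that disagrees. The registry content is not shown, so it cannot settle the matter here.

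A reader might also infer more than the documents support.

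- *A clash between 6 and 12 months.* The abstract and the Primary analysis, the two places that say when the outcome is judged, both say 6 months. The 12 months in the primary objective reads as the supplementation period, which the Interventions section also gives as 12 months. These are not two rival time points.
- *A much larger false-positive rate.* At 0.05 per test the same formula gives 9.75% for two outcomes and 14.26% for three, but the article nowhere states an alpha of 0.05.
- *No planning basis for either listed primary.* HbA1c has the target *d* of 0.4. Only FBG has none.
- *A flaw in the economic analysis.* The cost-effectiveness ratio uses fasting glucose, and the modelled analyses mention a primary trial outcome without naming it. An economic effect measure need not be the primary outcome, so changing it would be a preference.

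**Conclusion.** The protocol is wrong as written on one specific matter: the formal endpoint definition names FBG where the abstract, objective and primary analysis name IS, and the only outcome with a stated power is absent from both endpoint lists. The main consequence is that an FBG-only or IS-only result has opposite meanings in different sections. The numerical consequence is modest: about 2.0% rising to at most about 3.0%, assuming 0.01 per test, independence, and that all three outcomes are treated as candidates. The 2.0% comes from the either-outcome rule itself and would remain after the endpoint lists are corrected; it is a separate question. The sample size calculation is not in doubt, nor is the 6-month time of judgement.

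**What to change.** Before unblinding, reconcile the abstract, Primary objective, Primary endpoints, Secondary endpoints, Sample size and Primary analysis to one primary pair, and check that pair against the registered primary outcome. The pair supported by the abstract, objective and primary analysis, with IS also the sizing outcome, is HbA1c and IS, judged at 6 months. If the sponsor confirms it, the Primary endpoints section should read along these lines: *the primary outcomes are HbA1c and insulin sensitivity, each compared between groups at 6 months*. FBG would then appear in the secondary list only.

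If the registered outcome turns out to be FBG, the objective, sample size and primary analysis need to change instead, and FBG needs a stated difference, SD and power.

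For the HbA1c and IS pair, the cost is a wording amendment and a registry check. No extra data are needed if IS is derived from fasting glucose and insulin, which are already collected alongside HbA1c.

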#### Secondary endpoints

The following are secondary endpoints:Progression to diabetes mellitus (based on FBG or HbA1c)CVD risk factors, including, for example, FBG, plasma cholesterol, body weight, BMI, smoking, alcohol consumption, dietary intake, physical activity and blood pressureAcceptability of the supplements, as shown by pill counts and adverse effects.

### Sample size

The sample size is based on an estimated mean difference in IS of 0.3 (with SD of 0.7, equal to Cohen’s *d* of 0.4) between the intervention and control groups. We will need 164 participants per group to reject the null hypothesis that the intervention and control group means are equal with probability (power) 0.9 and type I error probability (α) of 0.01. Allowing up to 20% loss to follow-up over 1 year, we will need to recruit a total of 410 participants.

### Screening and recruitment

Participants will be screened and selected through the Diabetes Alliance network. Men and women aged 40–70 years with a diagnosis of PreDM will be invited to participate in the study. Informed consent, baseline measures and questionnaire responses will be obtained.

### Randomisation and blinding

Research staff will randomise participants into the study using permuted blocks of sizes 4 and 6, stratified by GP practice and biological sex (male or female), programmed into a computerised research electronic data capture (REDCap) database [21]. The allocation will be concealed and study personnel, the participants and the statistician will be blinded. The study coordinator will send out the capsules (labelled as A or B) to participants according to the allocation at baseline and every 3 months until 1 year. The adjudicators for adverse events will also be blinded to the allocation. Unblinding will occur at the close of the study unless a participant wishes to withdraw from the study or the GP requests unblinding of a participant for medical reasons, in particular for the diagnosis of T2DM.

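### Two arm-wide capsule codes combined with individual unblinding during the trial mean that one code break can reveal both arms to staff who see other participants' labels

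*Protocol article*

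**What the plan says.** The abstract of the protocol article promises that "The identity of the supplements will be blinded to both research personnel and the participants". The Randomisation and blinding section extends this to study personnel, participants, the statistician and the adverse event adjudicators.

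That section also sets the labelling: "The study coordinator will send out the capsules (labelled as A or B) to participants according to the allocation at baseline", and then at three-monthly intervals up to one year. Allocation is 1:1 between two arms, so each letter stands for one arm.

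The section then sets the unblinding rule: "Unblinding will occur at the close of the study unless a participant wishes to withdraw from the study or the GP requests unblinding". The GP's request is to be "for medical reasons, in particular for the diagnosis of T2DM". Progression to diabetes is also listed under Secondary endpoints.

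Under Data collection methods, participants return leftover capsules and an adverse event questionnaire every three months, and research staff use these for pill counts and adverse event records. No section mentions a code specific to a participant or kit, more than two letters, or a limit on who is told the result of a break.

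**The concern.** The labelling scheme and the unblinding rule work against each other. With a code shared by a whole arm, one participant cannot be unblinded in isolation. Learning that a participant on A received zinc also tells the reader that every other A is zinc and every B is placebo. The person who learns this stays blind to the others only if they never see another label.

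The coordinator has to handle the letters to send the right capsules. Research staff receive the returned capsules and, if these come back in their labelled containers, see the letters too. If either learns the result of a break, the stated blinding of study personnel no longer holds for the people closest to adherence and adverse event data. The named example of a trigger, a diabetes diagnosis, is also a secondary endpoint. A break may therefore be prompted by an outcome while other participants are still being followed.

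**Working it through.** **1. Inputs**
- Codes: two, one per arm (Randomisation and blinding).
- Participants: 410 (Sample size).
- Unblinding before close: allowed on withdrawal or GP request (Randomisation and blinding).
- Proportion unblinded during the trial: not given. Assumed here, from 0.1% to 2%.

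**2. The plan's own figure.** The planned total reproduces: 164 per group × 2 = 328, and 328 / (1 − 0.20) = 410. The labelling point rests on no other stated figure and does not alter this one.

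**3. What one break discloses**
- Two shared codes: the treatment of the person unblinded, plus the meaning of the letter for up to 410 − 1 = 409 others. This ceiling applies only to someone who sees all the letters once everyone is enrolled.
- Unique numbers not tied to the arm: 1 of 410.

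**4. How likely at least one break is.** If each participant is independently unblinded with probability *p*, then P(at least one) = 1 − (1 − *p*)^410.

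| Assumed *p* | Expected breaks (410 × *p*) | P(at least one) |
|---|---|---|
| 0.1% | 0.41 | 0.34 |
| 0.25% | 1.03 | 0.64 |
| 0.5% | 2.05 | 0.87 |
| 1% | 4.1 | 0.98 |
| 2% | 8.2 | more than 0.999 |

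At about one unblinding per 400 participants a break is more likely than not. At about four expected unblindings it is close to certain.

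**5. Who could then decode other participants**
- Coordinator: sends capsules by letter at baseline and every three months, so sees the letters. Exposed on learning a result.
- Research staff: count returned capsules and record adverse events. Exposed if the returns carry the letter and they learn a result.
- Participants: see only their own letter. Exposed only if someone tells them what it means.
- GPs: learn the result that they request, but capsules are mailed to participants and leftovers go back to research staff. The article does not show GPs seeing labels.

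**6. Which outcomes are exposed.** HbA1c, glucose and insulin come from blood tests at pathology providers, so trial staff do not judge them. Pill counts and adverse effects (the acceptability endpoint), efforts to retain participants, and self-reported diet and activity are more open to influence from staff who know the arm.

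**The case against.** The strongest reply is that the article does not say who performs a break or who is told the result. A condensed article may leave that to the full protocol, which could contain a firewall or kit numbers. The rule also speaks of unblinding a single participant, which may already mean that disclosure is confined. It stands that the spread of the result to staff is inferred. It does not remove the point, because the article states both the two-letter labelling and the in-trial unblinding. This is a stated scheme that sits badly with the stated blinding, rather than a detail left out.

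A reader might infer several stronger things that the document does not support:

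- **Blinding would be lost for everyone.** This does not follow. Participants know only their own letter, and GPs are not shown to see labels.
- **Diabetes diagnoses and drop-out make a break certain.** The Background gives 25% progression over 3–5 years. That is 1 − 0.75^(1/3) = 9.1% to 1 − 0.75^(1/5) = 5.6% a year, or about 37 to 23 of 410. The 20% allowance is 0.20 × 410 = 82 losses. Neither figure counts code breaks: a diagnosis needs a GP request, and someone who stops responding asks for nothing. The Background also credits lifestyle change with roughly halving progression, and the Discussion describes slower progression in Australia.
- **The break would come early.** The document gives no basis for timing. Follow-up blood tests fall at 1, 6 and 12 months, and efficacy is judged at 6 months, so some diagnoses would follow that participant's main measurement.
- **The blocks make allocations predictable.** Blocks of 4 and 6 within practice and sex might let staff guess the next letter. Before a break a letter says nothing about treatment. After one, it matters only for people not yet randomised. The effect is unquantified and secondary.

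**Conclusion.** The concern holds within limits. As written, one code break discloses the meaning of both letters to anyone who learns the result and sees other labels. That undermines the stated blinding of study personnel, most plausibly the coordinator and the staff who handle returned capsules and adverse event forms.

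The chance of at least one break is about 0.34, 0.87 or 0.98 if 0.1%, 0.5% or 1% of the 410 participants are unblinded. These rates are assumptions. Whether a break reaches the staff is also an assumption, since the article neither says that it does nor prevents it.

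The likely damage is to pill counts, adverse event recording, retention and self-reported behaviour. Direct assessor bias in the laboratory outcomes is limited. This should be fixed because the remedy is cheap, but it does not by itself invalidate the primary comparison.

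**What to change.** - Label supplies with a unique participant or kit number that does not indicate the arm. Over-label any remaining A/B stock before it is mailed.
- Have the supplier, or another party already outside study conduct, hold the list linking numbers to treatment.
- State that each code break is logged and returns only that participant's treatment, to the requester and not to trial staff.
- If the full protocol already does this, correct the sentence on A/B labels in the article to say so.

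The cost is some relabelling, a number to track at each mailing and a short amendment. Sample size and analysis do not change.
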